Although the results of this educational intervention were promising, there is evidence that interventions that are individually-tailored to ESRD patients’ needs and preferences may be even more successful at reducing racial disparities in completion of evaluation and receipt of LDKTs [34, 35]. In this manuscript, we describe the protocol of a new randomized controlled trial (RCT) to test the efficacy of a computerized *Your Path to Transplant* (YPT) educational program on decreasing racial disparities in LDKT. The RCT will determine, compared to a usual care education control group (UC) from the transplant center, whether Black, Hispanic, and White patients receiving YPT increase in their readiness to pursue LDKT and transplant knowledge, and whether they become more likely to complete transplant medical evaluation and pursue LDKT. It will also examine whether YPT’s effectiveness in changing LDKT decision-making and behavior is different between Blacks, Hispanics, and Whites. Finally, it will examine how known patient, family, and healthcare system barriers to LDKT act alone and in combination with YPT to affect Black and Hispanic patients’ transplant decision-making and behavior.

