To determine whether, compared to the UC group, Black, Hispanic and White patients receiving YPT are more likely to complete transplant medical evaluation and pursue LDKT 18-months post-baseline, regression models will be fit with: 1) only the treatment condition as a predictor; 2) race added-in as a covariate; 3) an interaction term between treatment and race. To examine whether the YPT’s effectiveness in changing LDKT decision-making and behavior is different between Blacks, Hispanics and Whites, comparisons will be made of proportional forward movement in readiness at 8 months post-baseline between Black, Hispanic and White patients in the YPT condition. Also, Black, Hispanic and White patients will be compared on three occasions (baseline, 4 months post-baseline, and 8 months post-baseline) to determine if access to YPT increases transplant knowledge differently for Black, Hispanic and White patients through this follow-up period and if the intervention has different effectiveness on the increase in proportion of living donors being evaluated for LDKT and increases in the proportion of LDKTs among Black, Hispanic and White patients 18-months post-baseline.

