Finally, to examine how known patient, family, and healthcare system barriers to LDKT act alone and in combination with YPT to affect Black and Hispanic patients’ decision-making and behavior around LDKT, the direct effects of key modifiable and non-modifiable variables known to affect disparities in receipt of LDKT (e.g., medical mistrust, quality of health insurance, physician recommendation to pursue LDKT) on readiness to pursue LDKT, transplant knowledge, completion of transplant evaluation, and receipt of LDKT will be adjusted for in regression models of YPT’s effect on these outcomes for Blacks and Hispanics separately. Then, interactions between YPT and these factors will be added to the models. Specifically, we will model each dependent variable first using the main effects of the barrier variables and of the YPT intervention, and then add two-way interactions between the intervention and the barrier variables. Similar models will be constructed for White patients. Based on these models, we will determine: (1) the estimated magnitude of racial differences between Black, Hispanic and White patients with and without access to the YPT for each outcome, and (2) which patient and care-related variables represent important confounding and modifying effects for explaining racial/ethnic differences in each outcome. These analyses will help elucidate whether the YPT achieves results by attenuating the impact of specific ‘causes’ of racial/ethnic disparities in LDKT.

Qualitative analyses will be performed to understand responses to key open-ended questions asked in the survey, particularly those around socioeconomic barriers to patients’ pursuit of transplant, potential solutions to barriers patients face in their transplant pursuit, and actions patients are willing to take toward LDKT and DDKT. Patients’ responses will be coded and analyzed to determine themes.

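### For 8-month readiness, whether YPT works differently by race is to be judged by comparing races within the YPT arm, which cannot separate a difference in effect from a difference under usual care

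*Protocol article*

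**What the plan says.** The Background of the protocol article sets an objective of finding out whether YPT's "effectiveness in changing LDKT decision-making and behavior is different between Blacks, Hispanics, and Whites". The Statistical analyses section takes this up again and attaches an analysis of 8-month readiness to it: "comparisons will be made of proportional forward movement in readiness at 8 months post-baseline between Black, Hispanic and White patients in the YPT condition".

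Three other parts of the same section bear on race.

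- **18-month outcomes.** For completing evaluation and pursuing LDKT, regression models are to be fitted in sequence with "1) only the treatment condition as a predictor; 2) race added-in as a covariate; 3) an interaction term between treatment and race". These use both arms.
- **Knowledge.** "Black, Hispanic and White patients will be compared on three occasions", with the purpose "to determine if access to YPT increases transplant knowledge differently for Black, Hispanic and White patients through this follow-up period". The text does not say whether the UC arm enters this comparison.
- **Barrier models.** Barrier variables "will be adjusted for in regression models of YPT’s effect on these outcomes for Blacks and Hispanics separately", with similar models for White patients. Readiness is among the outcomes. The interactions named are between YPT and the barrier variables. The section also promises estimates of racial differences with and without YPT for each outcome.

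**The concern.** Effectiveness is a contrast between YPT and UC. A difference in effectiveness between races is therefore a difference between such contrasts, and it needs both arms. The analysis assigned to 8-month readiness has only one.

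It can go wrong in two directions. If races would move forward at different rates under usual care, the comparison can declare that YPT works better in one race when it works equally well in all. If YPT raises the lagging groups to the level of the others, the YPT arm shows no racial difference, and the comparison suggests nothing happened when the gap has closed. Reducing racial disparity is the trial's purpose, and 8-month LDKT readiness is the outcome on which it is powered.

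Equal movement under usual care is not a safe default here. The Background reports about 20% of Black and Hispanic patients against 30% of White patients transplanted two years after wait-listing, and it lists additional barriers for the first two groups. Those are not readiness rates, but they show that the authors expect racial differences without the intervention.

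**Working it through.** **The identity.** Let u be a race's proportion moving forward under UC, and d the change in that proportion caused by YPT. The YPT-arm proportion is y = u + d. For any two races A and B:

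y(A) − y(B) = [u(A) − u(B)] + [d(A) − d(B)]

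The question concerns the second bracket. The planned comparison estimates the left side, which equals it only when u(A) = u(B).

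**Inputs from the protocol.** Power and sample size gives 10% in UC and 20% in YPT reaching the Action stage at 8 months, with 300 patients per arm. The implied odds ratio is (0.20/0.80)/(0.10/0.90) = 2.25. The protocol gives no figure for the racial comparison itself, so there is none to reproduce.

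**Assumptions not in the protocol.** (a) 100 patients per race per arm, an even split of 300. (b) UC rates by race, shown as a range. (c) The 10% and 20% for reaching Action stand in for forward movement, which is a different quantity. (d) The within-YPT test is a three-group chi-square test with 2 df at 0.05.

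**One case by hand.** Take UC rates of 7/7/15% (Black/Hispanic/White).

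- *Same odds ratio.* y = 2.25u/(1 − u + 2.25u) gives 14.5%, 14.5% and 28.4%, mean 19.1%. Noncentrality = 100 × [2(0.1448 − 0.1913)² + (0.2842 − 0.1913)²]/(0.1913 × 0.8087) ≈ 8.4. With 2 df this gives a rejection probability of about 74%; simulation gives 72%.
- *Same +10 points.* The rates are 17%, 17% and 25%, mean 19.7%. Noncentrality = 100 × [2(0.0267)² + (0.0533)²]/(0.1967 × 0.8033) ≈ 2.7, which gives 29%; simulation also gives 29%.

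**Simulated rejection rates of the within-YPT test when YPT works equally in every race**

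| UC rates, Black/Hispanic/White | Same odds ratio 2.25 | Same +10 points |
|---|---|---|
| 10/10/10% | 5% | 5% |
| 9/9/12% | 15% | 8% |
| 8/8/14% | 46% | 18% |
| 7/7/15% | 72% | 29% |

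In the same-odds-ratio scenarios, a two-arm interaction test on the log-odds scale rejects in 3% to 4%. In the same +10-point scenarios, a two-arm test on the risk-difference scale rejects in about 5%.

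**The opposite error.** Let UC be 7/7/15% and YPT 20% in all three races. The gains are 13, 13 and 5 points, so the effect differs and the gap closes. The within-YPT test rejects in 5% of trials; the log-odds interaction test rejects in 27%. With UC at 5/5/20% and YPT at 20% throughout, the within-YPT test still rejects in 5%, against 51% for the interaction on the risk-difference scale and about three in four on the log-odds scale.

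**The case against.** The strongest reply is that the plan as a whole does use the UC arm when it considers race. A reader of the 8-month sentence might infer that differential effect by race is studied inside the YPT arm throughout. The documents do not support that. The 18-month models contain a treatment-by-race interaction. The barrier models estimate YPT's "effect on these outcomes for Blacks and Hispanics separately", which requires UC patients, and readiness is one of those outcomes. The promised racial differences with and without YPT would let a careful reader see a gap close. All of this stands. It does not cure the 8-month readiness analysis, because no between-race test of YPT's effect on readiness is named anywhere, and the within-YPT comparison remains the analysis assigned to that question.

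Three further inferences go too far.

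- The knowledge comparison might be read as confined to YPT. The text is ambiguous, and knowledge is compared between YPT and UC at the same three occasions elsewhere in the section. It needs a clarifying phrase.
- Patients already in Action cannot move forward, so one might say that races with different baseline stages must differ by construction. That needs baseline stage by race and a definition of the denominator, and the protocol article gives neither.
- The within-YPT contrast might be said to measure background differences alone. It measures background plus any difference in effect.

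The magnitude is also open to challenge. The larger rates assume a common odds ratio, under which absolute gains differ (7.5 points from 7% to 14.5%, against 13.4 from 15% to 28.4%). Someone who thinks in absolute terms would call that unequal benefit. With equal absolute gains the rates fall to 8% to 29%. That is fair, and both sets should be read together; both exceed 5% whenever UC rates differ.

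**Conclusion.** The point holds for 8-month readiness and is wrong as written there. The comparison is valid for its stated question only if races move forward equally under usual care, an assumption the protocol does not state and its Background makes doubtful. In the scenarios where YPT works equally in every race, the chance of declaring differential effectiveness runs from 5% with equal UC rates to 29% (equal absolute gain) or 72% (equal odds ratio) with UC rates of 7/7/15%. When YPT closes the gap, it stays at 5%.

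The algebraic point rests on no assumption. The percentages rest on an even racial split and on assumed UC rates by race, so they illustrate the problem and do not predict this trial's error rate. The randomised YPT-versus-UC comparison that determines the sample size is not affected, nor are the 18-month interaction models.

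**What to change.** For 8-month LDKT readiness, replace the within-YPT comparison as the test of differential effectiveness with the treatment-by-race interaction (2 df) already planned at 18 months. Fit it by logistic regression to both arms, with baseline LDKT stage as a covariate. Report the YPT-minus-UC difference with its confidence interval within each race, so that the absolute scale is visible beside the odds scale. Keep the within-YPT racial comparison and label it descriptive.

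State that the by-race knowledge comparison uses both arms, through treatment-by-race-by-time terms. Leave the race-separate barrier models as planned: they match the stated aim, and pooling them with three-way terms would be a trade-off that this point does not require.

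The change is to analysis wording and needs no new data or visits. Its price is precision: the interaction is estimated less precisely than the within-arm difference, and its power is modest (27% in the 7/7/15% gap-closing example). That is a reason to put weight on the race-specific estimates and intervals and not to read a non-significant interaction as evidence of equal effect.

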## Background

Nationwide, there are approximately 615,000 patients with end-stage renal disease (ESRD), or kidney failure, a condition that necessitates renal replacement therapy through either dialysis or kidney transplantation to sustain life. Transplantation has clear survival and quality-of-life benefits for patients [1, 2] and can reduce national health-care costs [3]. Living donor kidney transplant (LDKT) is the optimal form of transplantation since it can occur more quickly than deceased donor kidney transplant (DDKT) [4, 5] and results in better graft survival [2] and better quality-of-life [6]. Because of the deceased donor organ shortage, most patients are now considering whether to receive kidneys from family and friends through LDKT.

Due to higher rates of diabetes and hypertension, the two primary causes of kidney failure [7], Blacks and Hispanics are 3.4 and 1.5 times more likely, respectively, to develop ESRD than their White or non-Hispanic counterparts [2]. Despite this, research has shown that, compared to Whites, Blacks and Hispanics are less likely to complete transplant medical evaluation [8–10], be placed on the waiting list or have longer wait times [11, 12], or receive DDKTs and LDKTs [2, 10, 13, 14]. Specifically, at 2 years post-wait-listing, approximately 20% of both Blacks and Hispanics had received transplants while 30% of Whites had (OPTN data as of 09/19/2014). Therefore, while increasing the rates of LDKT could increase the quality-of-life and decrease the mortality of all ESRD patients, this approach could have its greatest impact on Black and Hispanic patients’ lives.

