### Statistical analyses

All statistical tests will employ an intent-to-treat (ITT) approach wherein subjects will maintain their assignment to the treatment condition to which they were originally randomized regardless of whether they actually end-up receiving the planned interventions or not [56]. Multiple imputation of missing data will be used for the analyses [57]. The alpha level for all tests will be set at 0.05, and random effects models will be used to account for longitudinal measurement and linear regression employed for normally distributed outcomes, logistic regression for binomially distributed outcomes, and Poisson regression for count outcomes. The social, demographic, and other characteristics of patients who refuse to join the study or are never successfully contacted will be compared to those who do not to determine if the patient selection procedure has resulted in a biased sample. A similar analysis will be conducted to compare the patients who drop-out of the study to those who do not to determine if patient attrition has biased the sample.

To test whether, compared to the UC education condition, Black, Hispanic, and White patients receiving YPT increase in their LDKT readiness, we will first examine the proportion of individuals moving into the Action stage for readiness to accept a LDKT 8 months post-baseline between the YPT and UC conditions. For a more fine grained assessment of change in LDKT and DDKT readiness throughout the study, change by three occasions (baseline, 4 months post-baseline, and 8 months post-baseline) will be examined. To assess differences in transplant knowledge, DDKT/LDKT self-efficacy, and DDKT/LDKT decisional balance, comparisons between the YPT and UC conditions by these three occasions will be made to determine if the intervention increases transplant knowledge, DDKT/LDKT self-efficacy, and DDKT/LDKT decisional balance scales. Finally, differences in the number of small steps toward LDKT and DDKT will be examined at these three time points.

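### The proportion-of-LDKT question by race has no contrast on the proportion scale: the only both-arm treatment-by-race test is, by inference, a logistic interaction, which can be null while the absolute racial gap widens

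*Protocol article*

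**What the plan says.** All of this is in the protocol article.

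- **Aim.** The Background describes a test of the YPT "educational program on decreasing racial disparities in LDKT"; the Discussion repeats the aim. The only outcome rates by race are also in the Background: two years after wait-listing, "approximately 20% of both Blacks and Hispanics had received transplants while 30% of Whites had". These are for any transplant, not LDKT at 18 months.
- **Question.** Statistical analyses asks whether the intervention has different effectiveness by race on the proportion of living donors being evaluated and on "increases in the proportion of LDKTs among Black, Hispanic and White patients 18-months post-baseline". That sentence names no model, scale or null hypothesis.
- **Method.** The same section assigns "logistic regression for binomially distributed outcomes". For completing evaluation and pursuing LDKT at 18 months it fits three models in sequence: treatment alone, then race added, then "an interaction term between treatment and race".
- **Gap by arm.** The barrier analysis fits adjusted models for Black and Hispanic patients separately, with similar models for White patients. From these it will determine "the estimated magnitude of racial differences between Black, Hispanic and White patients with and without access to the YPT for each outcome". No scale is given, and no test or interval for the change in the gap.

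**The concern.** The question is worded as a difference between races in the increase in a proportion. The natural answer is a difference of risk differences: the YPT-minus-UC change in each race, compared across races, which is the same as the change in the absolute racial gap. A treatment-by-race coefficient in a logistic model compares odds ratios. When usual-care rates differ by race, which is the premise of the trial, and YPT has an effect, the two comparisons generally differ.

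At stake is how the trial's leading aim is reported. A non-significant or zero interaction could be written up as equal benefit by race, and one modestly favouring minority patients as a reduced disparity, while the difference in the proportion receiving LDKT has grown. This is separate from the planned comparison of readiness by race within the YPT arm, because it arises even when both arms and the interaction term are used.

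**Working it through.** The plan states no figure for the treatment-by-race test, so there is none to reproduce.

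**Inputs**
- Usual-care rates: 20% minority and 30% White (Background, any transplant, illustration only). Other rates below are assumptions.
- Odds ratio: Power and sample size expects 10% versus 20% in the Action stage at 8 months, which gives (0.20/0.80)/(0.10/0.90) = 2.25. This is a readiness effect borrowed for LDKT receipt, so it too is an assumption.
- Cell size: 900/(3 races × 2 arms) = 150, assuming equal race groups and record follow-up for all.

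**Step 1. Common odds ratio, so the logistic interaction is exactly zero.** With usual-care rate p and odds ratio OR, the YPT rate is p·OR/(1 − p + p·OR).
- Minority: 0.20 × 2.25/(0.80 + 0.45) = 0.45/1.25 = 36.0%, a gain of 16.0 points.
- White: 0.30 × 2.25/(0.70 + 0.675) = 0.675/1.375 = 49.1%, a gain of 19.1 points.
- Absolute gap: 10.0 to 13.1 points. Minority/White ratio: 20/30 = 0.67 to 36.0/49.1 = 0.73.

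**Step 2. Interaction favouring minority patients.** With a minority odds ratio of 2.40 against 2.25 for Whites, the minority rate is 0.48/1.28 = 37.5% and the gap is 49.1 − 37.5 = 11.6 points, still wider than 10.0. The gap stays at 10.0 only if the minority rate reaches 39.1%, a minority odds ratio of (0.391/0.609)/(0.20/0.80) ≈ 2.57.

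**Step 3. Other assumed usual-care rates, common odds ratio 2.25**

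| Minority / White, UC | Minority / White, YPT | Absolute gap (points) | Ratio |
|---|---|---|---|
| 5% / 10% | 10.6% / 20.0% | 5.0 to 9.4 | 0.50 to 0.53 |
| 5% / 15% | 10.6% / 28.4% | 10.0 to 17.8 | 0.33 to 0.37 |
| 10% / 20% | 20.0% / 36.0% | 10.0 to 16.0 | 0.50 to 0.56 |
| 60% / 75% | 77.1% / 87.1% | 15.0 to 10.0 | 0.80 to 0.89 |

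At low rates the absolute gap widens while the ratio improves. At high rates the absolute gap narrows.

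**Step 4. How often the tests would differ.** Simulation of 20,000 trials per scenario, 150 per cell, 2-df tests at 0.05: a likelihood-ratio test of the logistic interaction against a heterogeneity test of risk differences. Rates are White/minority under usual care.

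| UC rates | +10 points in every race: logistic / risk difference | Common OR 2.25: logistic / risk difference |
|---|---|---|
| 30/20 | 6% / 5% | 5% / 7% |
| 20/10 | 10% / 5% | 5% / 14% |
| 15/5 | 22% / 5% | 5% / 26% |
| 20/5 | 31% / 5% | 5% / 38% |

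With a smaller equal gain of 5 points, the logistic test rejects 5%, 7%, 12% and 16% of the time in the same four rows. With a common odds ratio of 1.5, the risk-difference test rejects about 6% to 13%.

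**Step 5. Precision of the absolute contrast.** For the Step 1 rates, SE = √[(0.20×0.80 + 0.30×0.70 + 0.36×0.64 + 0.491×0.509)/150] = √(0.850/150) = 0.075. The 95% interval is about ±14.8 points (1.96 × 0.0753) around a change in gap of 3.1 points, and power is about 7%.

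**The case against.** Four stronger readings are tempting, and the documents do not support them.

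- **That the plan states an equal-proportion null and then tests a different one.** The proportion sentence names no null or model. Linking it to the logistic interaction is a fair inference from the neighbouring sentences, since no other both-arm race test is given for these outcomes, but it is not a written contradiction.
- **That a widening gap would go unseen.** The barrier analysis plans to estimate racial differences with and without YPT for each outcome, including receipt of LDKT. What it lacks is a stated scale and any interval or test for the change in gap. It also takes the estimates from separate barrier-adjusted models by race.
- **That the interaction answers in the wrong direction.** This holds only on the absolute scale. In the low-rate examples the minority/White ratio improves, and at 60%/75% the absolute gap narrows as well. The article does not fix disparity on one scale: the Background uses proportions for transplant receipt and relative risks for developing ESRD. Nor must the two nulls always part when base rates differ and YPT works: 20% to 30% and 70% to 80% share a 10-point gain and an odds ratio of 1.71.
- **That the logistic test has a 22% to 31% false-positive rate.** That needs assumed minority rates of 5% that triple to 15%. At 30%/20% the excess is about one percentage point.

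It can also be said that effect scales and standardised estimates are normal content for a statistical analysis plan, which is not shown, and that no stated model is wrong. That stands as a limit on severity. The remaining point is that the article words a question on the proportion scale and, as far as it specifies a both-arm test, offers one on the odds-ratio scale.

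**Conclusion.** The point holds as an inexpensive improvement, not as an error in a stated analysis. When usual-care rates differ by race and YPT has an effect, a zero logistic interaction, or one modestly favouring minority patients, can coexist with a wider absolute gap in LDKT receipt. The illustration is 10.0 to 13.1 points at 20%/30% with a common odds ratio of 2.25, while the ratio moves from 0.67 to 0.73.

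The size in this trial is unknown, because the article gives no LDKT rates by race. The mismatch is small near 30%/20%, larger if minority rates are near 5%, and can reverse at high rates, which may matter for completion of evaluation. The illustrations borrow an any-transplant rate and a readiness odds ratio; the simulations and interval width also assume 150 patients per race-by-arm cell. The conclusion that the scales can disagree does not depend on those particular values.

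**What to change.** Keep the logistic models. In Statistical analyses, add for the 18-month binary outcomes, from the fitted treatment-by-race model:

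1. standardised 18-month proportions by race and arm;
2. the YPT-minus-UC risk difference in each race;
3. the change in the White-Black and White-Hispanic gaps, with 95% CIs by delta method or bootstrap;
4. beside these, the interaction odds ratio and the relative disparity (minority/White ratio) in each arm.

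State there that the increase-in-proportion question is read from the absolute contrast in item 3, that the racial differences with and without YPT in the barrier analysis are reported on a named scale, and that no conclusion about reducing the disparity rests on the interaction odds ratio alone. Settle this before results by arm are seen.

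The cost is a few sentences and a few lines of code on models already planned, with no new patients or data. There are two downsides. The scales may disagree, so the text must say which question each one answers. The absolute contrast will also be imprecise, so the report should emphasise the interval over the p-value and should not read a wide interval around zero as evidence that the gap is unchanged.
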